### 5. Participants and criteria

**Inclusion criteria:** Consecutive adult patients scheduled for ventral hernia repair (umbilical, incisional and epigastric hernia) and screened positive for at least 1 risky SNAP factor at least 4 weeks prior to the date of surgery are eligible for participation.

**Exclusion criteria:** Other ventral hernias, (para-stomal hernias as well as giant ventral hernias with defect > 8cm), pregnancy and breastfeeding, allergy/contraindications to pharmaceutical and nutritional support and exercise in STRONG, not able to give informed consent (e.g., age<18 years, severe mental illness, compromised consciousness, and language challenges), previous alcohol delirium/seizures and withdrawal of consent.

### 6. Risks, side-effects, and inconvenience

#### 6a) Considerations

Participation has only few risks such as side-effects of the well-established pharmaceutical support in the intervention group. The medicine administration follows the national guidelines, including the established indications for use. Side-effects are reported to the Health Authorities.

Collection and storage of sensitive data for patients may be followed by a risk of data leak. This risk is lowered by carefully following the Danish guidelines for each procedure. The study will be approved by the Danish Data Protection Agency, and data will be stored in the Redcap (as recommended by the Region) on secured and logged servers according to Danish regulations.

In addition, for the intervention group changing of lifestyle could be considered uncomfortable for some period, however, important efforts are taken to reduce this by information, patient education, motivational support and in case of quitting high alcohol intake and daily smoking also prophylaxis against possible withdrawal symptoms.

However, this seems to be balanced by the possible effect on the reduced risk at surgery on short term and a possible effect on health on longer term. Furthermore, the participants have access to 24 hours/7 days a week open hotline (e-mail or phone) to the clinical project staff.

All participants are free to use other healthcare services to support lifestyle changes during the study period if wanted. The patients are asked about this at the follow-ups.

There might be risks or side-effects not previously known. Therefore, we ask the participants to inform about experiences of health problems during the study period. If we identify new types of side effects, the participant will be informed in order to consider the continuation of participation.

### 6b) Discontinuation

Participant withdrawal: A participant may withdraw from the study at any time without this impacting on any future investigations and/or treatments at the site.

Individual participant discontinuation: The investigator may discontinue any participant's participation for any reason, including an adverse event, safety concerns or failure to comply with the protocol.

Discontinuation of entire study: The principal investigator has the right to terminate this study at any time. Reasons may include the following, but are not restricted to unsatisfactory fulfillment the design, participant enrolment, keeping the timeschedule, or agreement with the description in the application.

## 7. Sampling of blood and urine in our research biobank for biomarkers

All participants have blood and urine tests sampled at baseline and the four scheduled follow-ups for the identification of alcohol- and tobacco biomarkers (B-PetH, U-EtG and U-cotinine), for routine nutrition profile analyses (PI-Protein and PI-Albumin), and routine analyses on B-Hemoglobin, PI-ASAT, PI-Bilirubin as well as for measurement of possible new markers developed during the project period. In total 30 ml blood and 10 ml urine are sampled at each meeting (inclusion and the 4-5 follow-ups with 1-3 months between). Half of the samples is kept for the analyses of new biomarkers possible developed during the project period (see below).

The routine analyses are performed at the local centres. The analyses of the established biomarkers on tobacco and alcohol are performed together for one factor at a time, mainly after collection of all samples. Therefore, it is necessary to collect and store the samples (separated into 1.0 ml in 1.8 ml cryotubes at minus 80° C placed at [name] Bispebjerg-Frederiksberg Hospital) during the project period until analysed. The bio-marker analyses are expected to be performed at the Parker Lab, same address. Left-over samples in the individual tubes used for routine and marker analyses are destroyed immediately afterwards.

As mentioned above, new markers may be developed during the project period, and we would therefore keep half of the samples (i.e., 5x1 ml whole blood and 2x1 ml EDTA plasma, 2x1 ml citrate plasma, 2x1 ml serum, and 5x1 ml urine) stored for further analyses related to measurement of markers for risk reduction at surgery during the study period. Left-over samples will be destroyed after end of the study period (31.12.2033).

In addition, the participants are separately asked about giving informed consent to keep the possible left-over samples stored in a completely anonymised form for future and not yet specified research. It is understood that the samples can be used in future research only after approval from the Scientific Ethical Committee and the Danish Data Protection Agency. If the participants do not give

the separate informed consent, all biological material will be destroyed at the end of the project (as described above)

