| Smoking (n° cigarettes/day, Nutrition (intake), Alcohol (n° drinks/week), Physical activity (min/day) | X         | X                      | X                    | X                       |
| EQ-5D (HRQoL)                                                                                         | X         | X                      | X                    | X                       |
| Adverse events                                                                                        |           | X                      | X                    | X                       |
| Status (validated)                                                                             |           |                        |                      |                         |
| Blood + urine: Alcohol & Nicotine biomarkers, Hgb, Albumin, Protein, ASAT, Bilirubin                  | X         | X                      | X                    | X                       |
| Weight and bio-impedance, height,                                                                     | X         | X                      | X                    | X                       |
| Frailty score (weight loss, handgrip, walking test, exhaustion, level of activity)    | X         | X                      | X                    | X                       |
| ASA-score                                                                                             | X         | X                      | X                    | X                       |
| Postoperative complications                                                                    |           |                        |                      |                         |
| Complications /yes/no)                                                                                |           |                        | X                    | X                       |
| Clavien-Dindo grade and CCI                                                                           |           |                        | X                    | X                       |
| Stay in hospital                                                                                      |           |                        | X                    | X                       |
| Second surgery                                                                                        |           |                        | X                    | X                       |

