| 4                          | Benefits of short- and long-term lifestyle change              |
| 5                          | Continued change of lifestyles (handling risk of relapse)      |
| 6 and follow-up            | Continued education based on the current conditions            |
| + continued preoperatively | Continued education based on the current conditions            |

At each meeting we look into: The status and follow-up on the 'homework' via logbooks as well as challenges and successes. Patients are asked if they have experienced side effects of the pharmacological support. Potentially unknown side effects are reported and, if serious, may lead to early termination of the trial.

The specific physical activity includes 5 minutes respiratory exercise and 25 minutes activities chosen by the patient from a menu, thus adding up to 30 minutes per day. It starts on the first meeting and the patient walks through the complete 30 minutes program supported by the counsellor.

The specific nutrition program is adjusted to the patients individual need ensuring the complete intake required to change lifestyle in accordance with the individual needs.

The pharmaceutical support for smoking cessation intervention follows the national recommendations that have successfully been used in Danish studies of surgical patients. It is emphasized that the entire program is adapted to the individual patients - including guidance on supportive medicine - and that all pharmaceutical support is an offer. It includes personalised Nicotine Replacement Therapy (NRT) in accordance with the internationally acknowledged Fagerström test for nicotine dependency and patient preferences. Pharmaceutical support for risky drinkers also follows the national recommendations, successfully been used in Danish studies of surgical patients. It includes thiamine (300 mg daily) and combined B vitamins, alcohol withdrawal prophylaxis and treatment (chlordiazepoxide 10 mg as required in national guidelines) and low dose of disulfiram (200 mg × 2 weekly) supervised at weekly meetings (administered only if the patient has a negative alcohol breath test). The study medication is provided for free. The intervention group is followed during the intervention by additional measurements, Table 4.

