Table 4: Additional measurements in the intervention group related to the SNAP factors of the individual participants (AUD: Alcohol use disorder; AWS: Alcohol withdrawal symptoms; CIWA-aR: Clinical Institute Withdrawal Assessment for alcohol-revised; CO: carbon-monoxide; Diagnostic NRT: nicotine replacement therapy; TLFB: timeline-follow-back)

| Measurements
(Intervention group, exclusively) | Week1 | Week 2 | Week 3 | Week 4 | Meet 5 | Week 6+ |
|---------------------------------------------------|-------|--------|--------|--------|--------|---------|
| Motivation and reflections                        | X     |        |        |        |        |         |
| Adverse events                                    | X     | X      | X      | X      | X      | X       |
| Smoking                                    |       |        |        |        |        |         |
| Cigarettes per day (N°)                           | X     | X      | X      | X      | X      | X       |
| Tobacco dependence (Fagerström criteria)          | X     |        |        |        |        |         |
| Use of NRT (mg)/other craving reducing medicine   | X     | X      | X      | X      | X      | X       |
| Validation by CO concentration (breath)           | X     | X      | X      | X      | X      | X       |
| Nicotine biomarkers in urine                      | X     |        | X      |        | X      | X       |
| Alcohol                                    |       |        |        |        |        |         |
| Alcohol per week (units 12 g, TLFB)               | X     | X      | X      | X      | X      | X       |
| Alcohol dependency (AUD criteria)                 | X     |        |        |        |        |         |
| Alcohol concentration (breath test)               | X     | X      | X      | X      | X      | X       |
| Alcohol biomarkers (blood + urine)                | X     |        | X      |        | X      | X       |
| If withdrawal symptoms (CIWA-aR)                  | X     | X      | X      | X      | X      | X       |
| Use of AWS prophylaxis (mg)                       | X     | X      | X      | X      | X      | X       |
| Nutrition                                  |       |        |        |        |        |         |
| Food intake according to plan                     | X     | X      | X      | X      | X      | X       |

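### Urine cotinine, the only smoking validation common to both arms, cannot separate nicotine replacement from smoking, and the data needed to handle replacement users are collected in one arm and only up to surgery

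*Protocol*

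**What the plan says.** Chapter 7 states that "All participants have blood and urine tests sampled at baseline and the four scheduled follow-ups", and gives the purpose as "for the identification of alcohol- and tobacco biomarkers (B-PetH, U-EtG and U-cotinine". Table 1, the schedule for all included participants, lists under validated status "Blood + urine: Alcohol & Nicotine biomarkers, Hgb, Albumin, Protein, ASAT, Bilirubin". It also has self-reported cigarettes per day at every visit. It has no row for breath CO and none for use of nicotine replacement.

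Section 3c describes the pharmaceutical support for smokers in STRONG: "It includes personalised Nicotine Replacement Therapy (NRT) in accordance with the internationally acknowledged Fagerström test for nicotine dependency". This support is an offer, and study medication is free of charge. Table 4, which applies to the intervention group exclusively, adds "Validation by CO concentration (breath" and the dose of replacement used. Its columns run from Week 1 to Week 6+, and Table 2 shows that this last period is preoperative.

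Control patients may use support outside the project (sections 3a and 3c). Chapter 6a says that patients are asked about such use at the follow-ups.

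Improvement of risky lifestyles, self-reported and validated, is a secondary outcome (section 2a). The definition of successful risk reduction (Outcomes and data collection) refers to chapter 2 for how lifestyle is validated. Chapter 2 contains no cut-off and no rule for users of replacement.

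**The concern.** Cotinine is a breakdown product of nicotine, and Table 1 itself speaks of nicotine biomarkers. A patient who has stopped smoking but uses replacement can therefore test positive. This is general pharmacology, not a statement in the protocol. Replacement is part of the tested programme, so the error in the marker is tied to the allocated arm.

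Two measurements would resolve a positive result: breath CO and a record of replacement use. Both are scheduled in one arm and stop at surgery. A later analysis plan can write a rule, but it cannot recover data that were never collected.

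At stake are the validated smoking part of a secondary outcome in studies 1A and 1B, the dose-response studies 5A and 5B, and study 5C. In 5C, a truthful quitter on replacement could look like a patient who misreports.

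**Working it through.** **1. The plan's own figure.** The only related calculation is the sample size for complications, 20% against 10% (chapter 4). With a two-sided alpha of 0.05, 80% power and pooled variance:

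n = [1.96·√(2·0.15·0.85) + 0.8416·√(0.20·0.80 + 0.10·0.90)]² / 0.10² = (0.990 + 0.421)² / 0.01 ≈ 199 per arm.

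This matches the stated 2 × 199. It does not depend on the smoking marker. The protocol gives no figure for the validated smoking outcome, so there is none to reproduce.

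**2. What is scheduled, by visit** (Tables 1 and 4, chapter 7).

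| Visit | Cigarettes/day | Cotinine | Breath CO | Replacement use |
|---|---|---|---|---|
| Baseline | both arms | both arms | STRONG only | STRONG only |
| Week 6 / surgery | both arms | both arms | STRONG only | STRONG only |
| 1, 3 and 6 months | both arms | both arms | neither arm | neither arm |

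At surgery, a cotinine-positive patient on replacement can be recognised in STRONG but not in the control arm. After surgery, such a patient has no scheduled CO or specific replacement item in either arm.

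**3. Cotinine used alone: an illustration.** Let p1 and p2 be the true quit rates in STRONG and control, and f1 and f2 the shares of quitters on replacement at the visit. Suppose all of those patients test positive and are counted as smokers.

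Observed difference = p1(1 − f1) − p2(1 − f2).

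Inputs: p1 = 51% and p2 = 27% are the quit rates that section 2b reports from the group's earlier smoking and alcohol trial before cancer surgery. They are assumed here to be true rates. The protocol gives no values for f1 and f2, so they are varied. The true difference is 51 − 27 = 24 points.

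- f1 = 25%, f2 = 0: 38.25 − 27.0 = 11.25 points.
- f1 = 25%, f2 = 10%: 38.25 − 24.3 = 13.95 points.
- f1 = 25%, f2 = 25%: 38.25 − 20.25 = 18.0 points. With equal shares the difference shrinks in proportion and does not reverse.
- f1 = 50%, f2 = 0: 25.5 − 27.0 = −1.5 points.
- f1 = 50%, f2 = 10%: 25.5 − 24.3 = +1.2 points.

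The difference vanishes when f1 = 1 − p2(1 − f2)/p1:

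- f2 = 0: 1 − 27/51 = 47%.
- f2 = 10%: 1 − 24.3/51 = 52%.
- f2 = 25%: 1 − 20.25/51 = 60%.

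**4. Reclassifying STRONG patients only.** If Table 4 data restore all STRONG quitters (f1 = 0) while control quitters on outside replacement stay positive:

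- f2 = 10%: 51 − 24.3 = 26.7 points.
- f2 = 25%: 51 − 20.25 = 30.75 points.

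Both exceed the true 24 points, so the bias now favours STRONG.

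**The case against.** A reader might infer that STRONG quitters on replacement are classed as smokers. The protocol does not say so. It sets no cut-off and no abstinence algorithm, and such a rule is commonly left to the analysis plan. The absence of a rule is therefore not the point here. Up to surgery, moreover, STRONG patients on replacement can be recognised from Table 4. That part of the objection stands.

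A reader might also infer that the bias must run against STRONG. It need not. Controls may use outside support, and section 3b makes smoking cessation mandatory in standard care at two centres, so replacement use among control quitters should not be taken as zero. The size is also uncertain. The 51% and 27% come from a different surgical population, and the protocol does not say how they were validated. The replacement shares are assumed and need not be alike at surgery and at six months.

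Chapter 6a already plans a question to all participants about outside support. That helps, but it is not a specific item on current replacement use and does not appear in Table 1. Self-reported smoking is a co-listed outcome collected in both arms, and this point does not touch it.

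What the objection does not remove is the asymmetry in data collection, which no later rule can repair.

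**Conclusion.** The concern holds as a measurement gap. The protocol as written does not allow a validated abstinence rule that handles replacement users to be applied equally to both arms at surgery, or to either arm at 1, 3 and 6 months. Cotinine alone would bias the validated quit rate against STRONG if replacement use is sufficiently higher there. Correcting only the STRONG arm would bias it the other way.

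The size cannot be fixed from the protocol. The figures in the working show only that moderate replacement use could remove half of a 24-point difference and heavier use could hide it. They rest on assumed quit rates, assumed replacement shares and use of cotinine alone.

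The reach is limited to the validated smoking component of a secondary outcome and the studies that use it. Complications and the 2 × 199 sample size are unaffected. The change is worth making because it is cheap and the missing data cannot be recovered later.

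**What to change.** Add to Table 1 an item on current use of nicotine replacement, for smokers in both arms, at the surgery visit and at 1, 3 and 6 months. Making the chapter 6a question specific would do this. State one abstinence rule for both arms, under which a patient who reports abstinence, uses replacement and is cotinine-positive is not counted as a smoker on cotinine alone. Where feasible, also take the breath CO already used in STRONG in both arms at those visits, as a supplement to cotinine.

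The cost is one form item and, if CO is added, a brief breath test. CO detects only recent smoking. Without CO, the abstinence of replacement users rests on self-report, and the reports should say so. Nothing in the treatment of either arm changes.

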### 8. Collection of information from the medical records

Prior to informed consent (but after patient contact in relation to the present hernia pathway with the involved surgical clinics), the medical records are screened for diagnoses and SNAP factors. This information is used by the research group to identify possible participants to be informed about the study and for study 4. After informed consent, the patient characteristics of age, gender, diagnosis, planned treatment including surgery, co-morbidity, risk factors and present lifestyle profile as well as the descriptions of surgery and anaesthesia, the stay in hospital, possible complications and related intervention, conditions, re-admissions, visits in the out-patient clinic, and other similar activities in the perioperative period are collected. The consent gives the responsible researchers, the sponsor and representatives, and eventual supervisory authority direct access to obtain information in the patient's medical record, etc., (including electronic medical records), in order to see information about the participant's health, which is necessary as part of the implementation of the research project and for control purposes, including self-control, quality control and monitoring, which they are obliged to carry out.

### 9. Data Handling

#### 9a) Handling and storage

During the collection period, the data are stored at the secured Redcap in the Region H, as recommended. Data analyses are performed blinded and there will be no personal identification in presentation of results. After finalizing the project in 2033, all person identification including the project number will be deleted, so only the anonymous results will be kept for documentation. The study will before start be approved by:

- The Scientific Ethical Committee in Denmark.
- The Danish Data Protection Agency. The study follows the General Data Protection Regulation (GDPR, Databeskyttelsesforordningen) as well as the Data Protection Act (Databeskyttelsesloven). Data Processor Agreements are signed by the partners participating in data collection and bio-analyses.
- The protocol is registered at the [www.clinicaltrials.gov](http://www.clinicaltrials.gov).

### **10. Economy**

This is an investigator initiated clinical study.

The principal investigator [name] has received 5.0 million DKK from the Insurance Company Danmark for salary og project staff, nutritional and pharmaceutical support, and lab analyses. The grant is administered by the Bispebjerg-Frederiksberg Hospital, Region H.

Furthermore, the Novo Nordic Foundation has supported the project with a grant of 0.6 million DKK. The project staff has no relation to the grant-giving organization, which has no impact on the project.

The co-financing from the Parker Institute at Bispebjerg-Frederiksberg Hospital covers office facilities and administration as well as bio-banking.

### **11. Payments for participation**

There is no payment for participation.

